## Abstract

Fire Department of New York (FDNY) rescue and recovery workers exposed to World Trade Center (WTC) particulates suffered loss of forced expiratory volume in 1 s (FEV_1_). Metabolic Syndrome increased the risk of developing WTC-lung injury (WTC-LI)_._ We aim to attenuate the deleterious effects of WTC exposure through a dietary intervention targeting these clinically relevant disease modifiers. We hypothesize that a calorie-restricted Mediterranean dietary intervention will improve metabolic risk, subclinical indicators of cardiopulmonary disease, quality of life, and lung function in firefighters with WTC-LI. To assess our hypothesis, we developed the Food Intake REstriction for Health OUtcome Support and Education (FIREHOUSE), a randomized controlled clinical trial (RCT). Male firefighters with WTC-LI and a BMI > 27 kg/m^2^ will be included. We will randomize subjects (1:1) to either: (1) Low Calorie Mediterranean (LoCalMed)—an integrative multifactorial, technology-supported approach focused on behavioral modification, nutritional education that will include a self-monitored diet with feedback, physical activity recommendations, and social cognitive theory-based group counseling sessions; or (2) Usual Care. Outcomes include reduction in body mass index (BMI) (primary), improvement in FEV_1_, fractional exhaled nitric oxide, pulse wave velocity, lipid profiles, targeted metabolic/clinical biomarkers, and quality of life measures (secondary). By implementing a technology-supported LoCalMed diet our FIREHOUSE RCT may help further the treatment of WTC associated pulmonary disease.

## 1. Introduction

Metabolic Syndrome (MetSyn) is defined as having at least three of five risk factors (abdominal obesity, insulin resistance, hyperglycemia, dyslipidemia, and hypertension) that increase the likelihood of cardiovascular disease [1]. MetSyn afflicts more than 30 percent of adults (>47 million Americans) and is associated with impaired lung function [2,3]. Our group has focused on defining the development of World Trade Center-particulate matter (WTC-PM) associated lung disease in the context of MetSyn in the well-phenotyped Fire Department of New York (FDNY) Cohort [2,3,4,5,6,7,8,9,10,11].

Nearly half of chronic obstructive pulmonary disease (COPD) patients demonstrate the presence of MetSyn phenotypic characteristics [12,13,14]. Systemic inflammation, which is often seen in MetSyn, is implicated in lung function loss, the development of chronic obstructive airways dysfunction (OAD), vascular disease, and cancer [15,16,17,18,19]. Additionally, longitudinal investigations indicate that lower baseline forced expiratory volume in one second (FEV_1_) was an independent predictor of MetSyn [10,11]. Our recent investigations indicate that MetSyn components, most strongly dyslipidemia and abdominal obesity, are significant predictors of World Trade Center-lung injury (WTC-LI), as defined by FEV_1_ less than the lower limit of normal (LLN).

Although one major contributor to poor lung mechanics is from mechanical load-induced stress secondary to abdominal obesity, our prior work shows near equivalent contribution from dyslipidemia in those with WTC-LI [2,10,11]. Inflammatory profiles from serum samples collected within three months of 9/11 showed that dyslipidemia predicted WTC-LI even after adjusting for body mass index (BMI), and was in fact a stronger predictor than obesity [2,3,4,5,6,7,8,9,10,11,15,20,21]. In light of these findings, we focused our work on the inflammatory effects of lipids in the development of particulate matter (PM)-induced lung injury [22]

To investigate the potential reversibility of WTC-LI by direct impact on MetSyn risk factors, we focus on calorie-restricted (CR) Mediterranean diets based on recent studies showing their ability to attenuate lipid levels [20,23,24]. Modifying MetSyn through diet and exercise has been used successfully in other studies to directly impact lung disease. Dietary interventions in OAD patients improved FEV_1_ and forced vital capacity (FVC) by as much as 22 percent in as little as 15 days [25,26]. Using a low calorie diet, investigators achieved a 20 kg loss over a 6-month period, and found that every 10 percent relative loss of weight led to significant improvement of FVC by 92 mL and FEV_1_ by 73 mL [27]. It has been documented that patients with decreased BMI from 37 to 32 kg/m^2^ also had increased FEV1 and FVC [28].

Technology-supported behavioral interventions have shown enhanced data collection and improved adherence to diet plans [29,30]. Mobile technology allows clinicians to deliver targeted behavioral interventions and deliver counseling remotely, increasing scalability. We have previously developed an innovative weight loss intervention involving: (1) cloud-based self-monitoring of behavior (diet and physical activity) with automated feedback; (2) theory-based behavioral counseling delivered via WebEx (Cisco WebEx, Milpitas, CA, USA) group sessions; (3) standardized education to minimize calorie intake and enhance energy expenditure [29].

In the context of our prior findings, as well as the previously discussed literature linking nutritional modification to health benefits, we have chosen to explore the therapeutic potential of ameliorating MetSyn phenotype in our WTC-exposed cohort [2,3,4,5,6,7,8,9,10,11,21]. In the current study, we are implementing a technology-supported, low calorie Mediterranean (LoCalMed) dietary intervention to improve metabolic risk factors in subjects with WTC-LI. We hypothesize that our dietary intervention will have a therapeutic effect on the clinical endpoints of body mass index (BMI), FEV_1_, fractional nitric oxide (NO) concentration in exhaled breath (FeNO), pulse wave velocity (PWV), lipid profiles, targeted biomarkers and quality of life measures.

## 2. Methods

### 2.1. Design and Setting of the Study

FIREHOUSE is a 6-month randomized, controlled, two-arm, parallel, un-blinded, exploratory clinical trial, with 1:1 allocation, in overweight (specifically for this study our inclusion criteria was a BMI > 27 kg/m^2^) FDNY firefighters with documented WTC-LI (defined as FEV_1_ < LLN post exposure). While overweight is defined as having a BMI of 25.0 to <30.0 kg/m^2^, and subjects are considered obese if there BMI is ≥30.0 kg/m^2^ [31], for the purposes of our study we wanted to enroll subjects that were overweight with a BMI that was greater than 27 kg/m^2^. This was by design since our power analysis and primary outcome assessment was targeting at least 1–2 units of BMI change in the intervention group [32,33,34,35].

Ethics: The trial and all proposed analysis will be performed in accordance with the New York University (NYU)-Institutional Review Board, Protocol 17-00127.

#### 2.1.1. Participant Characteristics

Inclusion and exclusion criteria for study enrollment detailed in Table 1. In brief, participants are eligible for inclusion if they are FDNY firefighters with documented WTC exposure, enrolled in the FDNY WTC-health program (WTC-HP), and have WTC-LI as defined by an FEV_1_ < LLN after exposure, Table 1 and Figure 1. This FIREHOUSE trial will be performed in accordance with the Declaration of Helsinki and Good Clinical Practice and the protocol is approved by the New York University IRB #17-00127.

Participant recruitment will include: (1) direct mailings; (2) telephone contact; (3) email; (4) self-referral. Recruitment efforts will be supported by a study website that provides general information about the study and answers frequently asked questions. The website will also facilitate study activities during the intervention period.

Participants will be randomized to either Usual Care (control arm) or LoCalMed diet plus technology-assisted nutrition education and behavior modification (intervention arm), Figure 2. Each study arm is active for six months following enrollment. Participants will return after six months for a repeat of all measures. All participants will be informed of pertinent clinical assessment conclusions and offered all of the intervention materials at the study’s conclusion, Table 2 and Table S1.

#### 2.1.2. FIREHOUSE Intervention Usual Care Group

The Usual Care group serves as a control (reference) arm, with target enrollment of *N* = 70. In addition to standard care from their WTC-HP primary provider, participants in the Usual Care group will receive newsletters every five weeks during the intervention from study staff related to: (1) mindfulness; (2) sleep; (3) staying healthy year-round; (4) disease self-management. As an added incentive for remaining in the study, Usual Care participants will be provided access to educational and behavioral materials upon completion of their 6-month measurement visit. The LoCalMed group will be enrolled in a 6-month, technology-supported, educational-behavioral program designed to promote a calorie-restricted, Mediterranean-style diet and regular, moderate-intensity physical activity. At baseline, participants will be provided in-person, group-based technology training, and will receive handouts with the following study goals: (1) weight loss of ≥seven percent at 6-months; (2) saturated fat intake ≤seven percent of kcal; (3) ≥150-min per week of moderate-intensity physical activity. After the initial technology training session, all intervention-related activities will be delivered remotely via smartphones. The LoCalMed program will consist of two main parts: (1) mobile self-monitoring with feedback; (2) remote group-based education and behavioral counseling.

##### Mobile Self-Monitoring

Participants will be provided a 6-month subscription for the commercial diet diary application MyNetDiary (MND, MyNetDiary, Inc., Marlton, NJ, USA) and directed to record their body weight weekly, all food and drink consumption, and any physical activity as it occurs. If needed, participants are provided with a digital bathroom scale for monitoring body weight during the intervention.

Self-monitoring of health behaviors (e.g., diet) and outcomes (e.g., body weight) is thought to promote behavioral change in part by bringing these factors to individuals’ conscious attention, thereby enhancing vigilance. In addition to providing a digital platform for self-monitoring, MND generates real-time feedback on nutrient intakes across foods, meals, and meal-days, as well as daily and weekly summaries of recorded physical activities. The multi-level organization of data in MND assists with information processing, which may reduce information burden that can lead to oversimplified heuristics (aka “food rules”) and burnout. To further limit information burden, MND nutrient output will be restricted to track only calories and macronutrients (carbohydrates, protein, and total, saturated, monounsaturated, and polyunsaturated fats). MND summary reports are updated with new entries, they will permit ecological momentary assessment (EMA) of behaviors at the time, which is thought to augment the effectiveness of self-monitoring.

Adding to the automated feedback provided by MND, the study dietitian will review the participants’ MND accounts weekly for the first four weeks and every second week thereafter during the intervention, and they will provide feedback reports via the participant’s personal (or a study-provided) email account. Reports will contain three parts: (1) adherence to self-monitoring; (2) body weight; (3) saturated fat intake. Feedback on saturated fat is graded as green (≤seven percent of kcal), yellow (>7–10 percent of kcal) or red (>10 percent of kcal), and it includes tailored advice on restricting saturated fat based on participants’ MND records. Within the program, reported body weights are plotted on a personalized weight loss trajectory line graph that is modeled with 95 percent confidence intervals to achieve a seven percent weight loss over six months [36]. In our experience, participants are motivated by the additional accountability that is provided by external monitoring of health behaviors and outcomes by study staff.

##### Education and Behavioral Counseling

Participants will receive group-based education and behavioral counseling (~1-h) each week for the first four weeks, and every other week thereafter during the intervention via the videoconferencing application, WebEx (Cisco WebEx, Milpitas, CA, USA). Group sessions are facilitated by the study dietitian, and anchored by brief animated videos (Powtoon, London, UK), Table 3. After each session, videos will be posted on the study website, which participants can access via a password-protected Brainshark link (Brainshark, Inc., Waltham MA, USA). Brainshark is a video viewing platform that records time spent watching videos and will help assess intervention dose.

Education videos in Table 3 were designed to provide intervention subjects materials for following a calorie-restricted, Mediterranean-style diet, and engaging in regular moderate-intensity physical activity, Table 3. The Mediterranean diet was selected as the dietary pattern for this intervention because of the emphasis on healthy fats. Previous metabolomics analysis of FDNY 9/11 first responders with and without WTC-LI suggested that metabolic pathways affected by dietary fats were risk factors for the condition [22]. This dietary pattern, which promotes whole fruits and vegetables, whole grains, nuts, legumes, fish, healthy oils (namely olive oil), and a limited amount of lean meat and low-fat dairy products, is largely consistent with dietary patterns that are commonly used in weight loss. To assist participants in restricting energy intake, additional education is provided on portion control, meals away from home, meal skipping, and avoiding empty calories (e.g., sugar-sweetened beverages), Table 3.

Behavioral counseling and videos are based on social cognitive theory (SCT), which focuses on the roles of self-referent thought and self-efficacy (i.e., confidence) in adopting and maintaining healthy behaviors. According to SCT, self-efficacy can be derived from four factors: (1) mastery experiences: goal-setting, prior successes, and problem-solving; (2) social modeling: learning by observing others; (3) verbal persuasion: encouragement from others; (4) physiological benefits: improvements in health outcomes (e.g., weight loss), Table 3.

Primary Outcome Assessment is a seven percent decrease in total body weight with a subsequent drop in BMI of roughly 1–2 kg/m^2^ depending on the individual’s height.

Secondary outcome measures include a 7–10 cc increase in FEV_1_ after trial intervention compared to control subjects, as well as an increased lean body mass relative to fat percentage on body-impedance analysis (BIA), reduction in PWV and FeNO, and improved perceived health status as measured by the Short Form 36 (SF-36) and the St. George’s Respiratory Questionnaire (SGRQ), which are both validated quality of life assessment tools available for public use. Details of the primary and secondary endpoints of the FIREHOUSE trial are shown in Table 4.

Additionally, we will collect clinical measurements such as routine vital signs, electrocardiograms (ECGs), routine chemistries, complete blood counts (including white blood cell differentials), liver function tests, and blood lipid profiles. Furthermore, we will collect saliva and stool samples for genomic (ORAgene-Discover; OGR-500; DNAgenotek) and microbiomic analysis (OMNIgeneGut; OMR-200 DNAgenotek), respectively.

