#### Sample Size and Interim Analysis

The primary objective is to compare the change in BMI in the two groups from pre-intervention to post-intervention after six months (intervention completion). The analysis for this primary objective will be based on the multivariate linear regression with adjustment for potential confounders. The difference for the change of BMI between the two groups will be estimated, and a corresponding 95 percent confidence interval will be calculated.

The sample size of the FIREHOUSE trial was estimated by the power analysis for the primary outcome of the change in BMI predicted between the start and end of the intervention, which was based on a two-sample test to compare the outcome between two groups under 1:1 randomization. According to the preliminary data, we assumed SD = 2 kg/m^2^ and the means of two groups “Usual Care” and “LoCalMed” to be 0 and −1 kg/m^2^, respectively. Furthermore, 6-month interventions with similar calorie targets and behavioral modification with exercise produce a 7–10 percent weight loss [37,38]. A total sample of 128 subjects (64 subjects in each arm) can achieve 80 percent power at α = 0.05. We will recruit 140 subjects accounting for potential loss of around 20 percent drop out.

The interim analysis plan will incorporate two interim looks and one final look, with all looks named as formal interim analysis, Table 5. This study will not be monitored for futility. The first look will be conducted at the completion of 6-month intervention or observation for 30 subjects in each group. This look will use 2-sided α < 0.001. The second look will be one formal interim look, which will be conducted at the completion of 50 subjects in each group with a 2-sided α = 0.007. The final analysis will take place at completion of all subjects in each group, with an O’Brien Fleming boundary for a 3-look design with 2-sided α = 0.033, Table 5 and Figure S1.

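### LoCalMed is counselled in groups and Usual Care is not, but neither the stated primary regression nor the sample size allows for correlation within counselling groups

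*Protocol article*

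**What the plan says.** Delivery differs by arm. Under Education and Behavioral Counseling, "Participants will receive group-based education and behavioral counseling (~1-h) each week for the first four weeks", then every second week by videoconference. Table 3 lists 14 sessions from week 1 to week 24, and section 2.1.2 adds group-based technology training at baseline. The same counselling section bases the programme on social cognitive theory and names among its factors "social modeling: learning by observing others", together with encouragement from others. In the control arm, section 2.1.2 says "participants in the Usual Care group will receive newsletters every five weeks during the intervention from study staff", on top of standard care; no group sessions are described.

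Other parts of LoCalMed are common to the arm or individual. "Group sessions are facilitated by the study dietitian, and anchored by brief animated videos", so there appears to be one facilitator and one set of videos. Under Mobile Self-Monitoring, "the study dietitian will review the participants’ MND accounts weekly for the first four weeks and every second week thereafter", with feedback sent to each participant.

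On analysis, Sample Size and Interim Analysis states: "The analysis for this primary objective will be based on the multivariate linear regression with adjustment for potential confounders". The sample size rests on a two-sample test with SD 2 kg/m², group means 0 and −1 kg/m², 80% power and α = 0.05, giving 64 per arm. Table 5 sets bounds of 3.951, 2.686 and 2.129 at 30, 50 and 70 completers per group, with an overall two-sided α of 0.036. The article mentions no group term, ICC, group size, number of groups or rule on group membership.

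**The concern.** This is a partially nested design: individual randomisation, with clustering created by treatment in one arm only. Where members of a counselling group influence each other, their BMI changes share a group component. The LoCalMed mean then varies more than the same number of independent subjects would imply. A regression with no group component understates that variance. The confidence interval for the primary difference is then too narrow, and the Table 5 bounds no longer deliver their error rate. The sample size has the matching weakness: if the variance is later computed correctly, 64 per arm no longer gives 80% power. A programme meant to work partly through peers should not take independence among those peers for granted.

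**Working it through.** **The plan's own figure.** With difference 1, SD 2 and two-sided α 0.05, the normal approximation gives 63 per arm. The two-sample t-test has power 0.795 at 63 and 0.801 at 64 per arm. So 64 is exact for independent subjects and contains no design effect.

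**Inputs.** From the article: SD 2, difference 1, 64 per arm, the Table 5 bounds and look sizes. Assumed, because the article gives neither: group size m and ICC, with equal-sized groups of fixed membership.

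**Formulas.** With nesting in one arm and equal arm sizes:

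- Design effect in LoCalMed: DE = 1 + (m − 1) × ICC
- Variance ratio of the difference, true to naive: v = (1 + DE)/2; standard error ratio f = √v
- Type I error at the final bound, naive test: 2 × [1 − Φ(2.129/f)]
- Power at 64 per arm with the correct variance, two-sided 0.05: Φ(1/(2f√(2/64)) − 1.96)
- Subjects per arm to restore 80% power: 64 × v, rounded up

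**Worked case, m = 10, ICC 0.05.** DE = 1 + 9 × 0.05 = 1.45; v = 2.45/2 = 1.225; f = 1.107. Final bound: 2.129/1.107 = 1.924, two-sided error 0.054. Power: 2.828/1.107 − 1.96 = 0.596, so Φ = 0.72. Per arm: 64 × 1.225 = 78.4, so 79.

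The three-look error comes from simulation (2 million runs, Table 5 bounds, looks at 30, 50 and 70 per arm, the same f at each look).

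| m | ICC | DE | f | Final look (nominal 0.033) | Three-look error | Power at 64 per arm | Per arm for 80% |
|---|---|---|---|---|---|---|---|
| any | 0 | 1.00 | 1.00 | 0.033 | 0.035 | 0.81 | 64 |
| 5 | 0.01 | 1.04 | 1.01 | 0.035 | 0.037 | 0.80 | 66 |
| 10 | 0.02 | 1.18 | 1.04 | 0.041 | 0.044 | 0.77 | 70 |
| 10 | 0.05 | 1.45 | 1.11 | 0.054 | 0.058 | 0.72 | 79 |
| 15 | 0.10 | 2.40 | 1.30 | 0.102 | 0.11 | 0.58 | 109 |

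The power column uses the normal approximation, hence 0.81 rather than 0.80 in the first row. The last row marks the edge of the assumed range; nothing in the article points to it.

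**Whether a group effect can be estimated.** With groups of 10 there are about 30/10 = 3, 50/10 = 5 and 70/10 = 7 groups at the three looks. The Satterthwaite degrees of freedom are (V₁ + V₂)² / [V₁²/(k − 1) + V₂²/(n − 1)], with k groups, n = 10k, V₁ = DE/n and V₂ = 1/n. At ICC 0.05 this gives about 5.5, 11 and 16. The t critical values matching the Table 5 p-values are then about 10.4, 3.29 and 2.32, against 3.951, 2.686 and 2.129. A group variance from three groups is barely estimable, so the fix should treat the interim looks differently from the final one.

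**The case against.** A reader might infer that the standard errors are too small and that the type I error does exceed the boundary. The article does not support that as fact. It gives no ICC, group size, number of groups or statement that membership is fixed, and at ICC 0 nothing is inflated.

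A reader might also infer that the regression is fixed as one with independent errors. Independence is explicit only in the sample-size test. For the regression, "will be based on the multivariate linear regression with adjustment for potential confounders" is the ordinary name of an independence model, but no variance estimator is stated. The article condenses a fuller protocol, and an analysis plan that is not at hand might add a group term or robust variance, or show that group identity is recorded.

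The sources of correlation are also narrower than they look. Shared lesson content is common to the whole arm and creates no variance between groups. Calendar time is shared with Usual Care subjects enrolled in the same period. A single dietitian, standard videos and individual diary feedback all limit group-to-group differences. If the programme affects nobody and groups are not formed on prognosis, it induces no correlation. Inflation needs a zero average effect with real variation between groups; with a non-zero average effect, such variation makes the interval too narrow. The trial also calls itself exploratory.

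All of this stands, and it bears on the size of the problem. It does not remove the mismatch between the design and the stated method: peer interaction is intended in one arm only. Nor could a later analysis plan restore power lost through an independence-based sample size.

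**Conclusion.** The point holds conditionally. The protocol names a linear regression and an independence-based sample size for a partially nested design, and allows for group correlation in neither.

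The consequence ranges from none at ICC 0, through a trivial excess with small groups and ICC 0.01, to a three-look error of about 0.058 with groups of 10 and ICC 0.05. Under the same bounds, independent subjects give about 0.035. Power at 64 per arm under a correct variance falls to about 0.77 (ICC 0.02) or 0.72 (ICC 0.05) with groups of 10. There is no spare sample to absorb this: 140 recruited with the stated 20% dropout leaves 140 × 0.8 = 112, below the 128 required even under independence.

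These figures rest on assumed group size and ICC, equal groups and fixed membership. Confidence that inflation would occur is moderate: peer interaction makes some correlation plausible, but the article gives no evidence of its size.

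**What to change.** - Record each LoCalMed subject's counselling-group ID, and state the planned group size and whether membership is fixed. Without the ID the analysis may not be repairable later.
- At the final analysis, fit the primary model with a random group effect in the LoCalMed arm only: Usual Care subjects as singletons, arm-specific residual variances, and Satterthwaite or Kenward-Roger degrees of freedom.
- At the interim looks, where there may be only 3 to 5 groups, keep the stated regression. Before any efficacy claim, report how the test statistic changes over a pre-stated ICC range, by dividing the naive Z by f. For m = 10 and ICC 0.05, the naive Z would need to reach 3.951 × 1.107 = 4.37 at look 1 and 2.686 × 1.107 = 2.97 at look 2 to meet the Table 5 bounds.
- Restate power over the same ICC range, including zero.

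The cost is one recorded variable and a different model statement. The confidence interval will be wider, and power will be below the stated 80% if the ICC is above zero. With few groups, the small degrees of freedom reduce power beyond the figures shown above.
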